### Course of study

The beginning of the study is scheduled for the 29th gestational week. Every study participant receives access to the *mindmom* app. Participants of both groups (IG and TAU) are requested to complete digital assessments, which are scheduled every 2 weeks for the period of the intervention (visits 1–5), as well as 1 and 5 months postpartum (visits 6 and 7). The assessments are completed via the *mindmom* app and contain self-report questionnaires, sociodemographic and medical data, physiological measures, and morning cortisol profiles, which will be sent to the responsible study center by post. Table 2 provides an overview of the visit schedule and its content. Moreover, all study participants have access to an online pregnancy guidebook embedded in the mindmom app that provides valid information about pregnancy and birth on a weekly basis. Women in the TAU group are encouraged to participate in regular antenatal care and are conveyed to mental health care services, if required. The IG participates in the eMBI. Figure 1 shows the flow chart of the mindmom study. Figure 2 shows the schedule of enrolment, interventions, and assessments of the mindmom study.

**Table 2 Tab2:** Study outcomes

	Time of assessment	Study outcomes	Instruments
**T1**	28th gestational week	• Symptoms of depression and (pregnancy-related) anxiety • Maternal-fetal attachment • Quality of life • Mindfulness • Morning cortisol profile • Sociodemographic variables (age, educational level, family status, income, occupation, number of children) • Medical history (gravidity, parity, fertility treatment) • Blood pressure, pulse, height, weight	EPDS, STAI, PRAQ-R MFAS EQ-5D FFA-14
**T2**	30th gestational week	• Symptoms of depression and (pregnancy-related) anxiety • Blood pressure, weight	EPDS STAI, PRAQ-R
**T3**	32nd gestational week	• Symptoms of depression and (pregnancy-related) anxiety • Maternal-fetal attachment • Quality of life • Blood pressure, weight	EPDS STAI, PRAQ-R MFAS EQ-5D
**T4**	34th gestational week	• Symptoms of depression and (pregnancy-related) anxiety • Blood pressure, weight	EPDS STAI, PRAQ-R
**T5**	36th gestational week	• Symptoms of depression and (pregnancy-related) anxiety • Maternal-fetal attachment • Quality of life • Mindfulness • Morning cortisol profile • Blood pressure, weight	EPDS STAI, PRAQ-R MFAS EQ-5D FFA

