**T6**	1st month postpartum	• Symptoms of depression and anxiety • Postpartum bonding • Satisfaction with medical care around the birth • Satisfaction birth • Breast feeding behavior • Blood pressure, weight • Medical details on current birth	EPDS, STAI PBQ-16 PEQ-G
**T7**	5th month postpartum	• Symptoms of depression and anxiety • Postpartum bonding • Mindfulness • Blood pressure, weight • Breastfeeding behavior • Morning cortisol profile • Technical handling and acceptance of the *mindmom* app	EPDS, STAI PBQ-16 FFA-14
**T1–7**	Continuously	• Out-of-pocket payments for alternative diagnostic and therapeutic methods, homeopathic products or non-prescription drugs	Cost diary

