#### Measures for cost-effectiveness

Health care service use and costs for both groups will be measured by means of secondary claims data of the statutory health insurers. This includes direct costs such as general and specialist care, medication, hospitalization, therapeutic products, medical aids, and other services related to pregnancy as well as costs associated with absenteeism. Further, the out-of-pocket costs by families will be assessed using a specific self-completing cost diary.

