Moreover, data will be analyzed by multi-level modeling. Hereby, the repeated measures (level 1) will be nested in the patients (level 2). A simulation study shows that only small samples on level 2 (< *n* = 50) lead to biased estimations of the standard errors on level 2 [58]. Expecting invariant results, the exploratory application of these models can increase the assurance regarding the exclusion of small between subject effects.

In accordance with the ICH Guideline E9, the primary analyses are performed according to the intention-to-treat (ITT) principle. Per-protocol (PP) analyses on sensitivity of effects are implemented in an exploratory fashion.

In order to reliably estimate missing values and thus to protect the analyses against response and selection biases, multiple imputations will be used [59]. First of all, missing values will be tested by Little’s Missing-Completely-At-Random test [60]. Following a negative result, *n* = 20 data sets with all variables of the analytic model are estimated. Hereby, value estimations are restricted to scale-specific ranges. Results are then pooled over the *n* = 20 data sets.

In accordance with the methods proposed by the German Institute for Quality and Efficiency in Health Care (IQWiG), the cost-effectiveness analysis will be carried out from the perspective of the statutory health insurance and, if possible, additionally include a societal and/or individual perspective [61]. The incremental cost-effectiveness ratio (ICER) will be calculated dividing the difference in costs by the difference in health benefit of the intervention compared to standard care. Costs are assessed in monetary units, and the benefit is measured by the primary (severity of symptoms) and secondary outcomes (f. e. cesarean sections, health related quality of life). The perspective of the analysis thereby determines the relevant cost components.

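### EQ-5D is last measured at 36 weeks' gestation, so the planned quality-of-life ICER has no utility data at or after birth, while diary costs run to 5 months postpartum

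*Protocol article*

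**What the plan says.** All references are to the protocol article.

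- **Benefit side.** Data analyses defines the ICER as the cost difference divided by the difference in health benefit, and says that "the benefit is measured by the primary (severity of symptoms) and secondary outcomes (f. e. cesarean sections, health related quality of life" supply the benefit. It gives no time horizon and no rule pairing a cost period with each benefit measure.
- **EQ-5D schedule.** In Table 2 (Course of study) the T1 instruments are "EPDS, STAI, PRAQ-R MFAS EQ-5D FFA-14". Quality of life and the EQ-5D appear again at T3 and T5 (32nd and 36th gestational week). At T6, 1 month postpartum, the instruments are "EPDS, STAI PBQ-16 PEQ-G". At T7, 5 months postpartum, they are "EPDS, STAI PBQ-16 FFA-14", and the T7 outcomes begin "Symptoms of depression and anxiety • Postpartum bonding • Mindfulness • Blood pressure, weight • Breastfeeding behavior • Morning cortisol profile". Neither postpartum visit lists quality of life or the EQ-5D.
- **Cost side.** The last row of Table 2 has a cost diary kept continuously over T1–7 for "Out-of-pocket payments for alternative diagnostic and therapeutic methods, homeopathic products or non-prescription drugs". Measures for cost-effectiveness adds that "Health care service use and costs for both groups will be measured by means of secondary claims data of the statutory health insurers", including hospitalization and absenteeism. No period is given for the claims data.
- **Perspective.** The base case is the statutory health insurance. A societal or individual perspective is added only if possible.

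**The concern.** An ICER is interpretable when costs and benefits cover the same period. Here the quality-of-life measure stops before birth for nearly all women, while at least one cost stream continues for months after it. Under Objectives, the trial expects effects on the birth experience, attachment to the newborn, the number of cesarean sections and the prevalence of peripartum depression. Any change in quality of life that follows from these would fall where no utility is recorded. Cost-effectiveness is part of the stated aim, and utility that was never collected cannot be supplied by any later analysis text.

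**Working it through.** **1. Is the missing postpartum EQ-5D a table-reading artefact?** Table 3 offers a check. It lists four exploratory 2 × 3 ANOVAs and one 2 × 2 ANOVA. Counting assessments in Table 2:

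| Outcome | Visits | Count |
|---|---|---|
| MFAS | T1, T3, T5 | 3 |
| EQ-5D | T1, T3, T5 | 3 |
| FFA-14 | T1, T5, T7 | 3 |
| Cortisol | T1, T5, T7 | 3 |
| PBQ-16 | T6, T7 | 2 |

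Four outcomes have three measurements and one has two, exactly as Table 3 states. The article's exploratory error rate also reproduces: 4 + 1 + 1 + 3 = 9 tests, and 1 − 0.95^9 = 0.37. A postpartum EQ-5D would break the count of four, so the schedule is as it reads.

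**2. Length of the two windows.** Inputs: T1 at 28 weeks, T5 at 36 weeks and T7 at 5 months postpartum (Table 2 and Course of study). Gestational age at birth is not given; I assume 40 weeks, with a range of 37 to 42.

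- EQ-5D span: 36 − 28 = 8 weeks.
- Five months: 5 × 365.25 / 12 / 7 = 21.7 weeks.
- Diary span: (40 − 28) + 21.7 = 33.7 weeks. Birth at 37 weeks gives 9 + 21.7 = 30.7; birth at 42 weeks gives 14 + 21.7 = 35.7.
- Share of the diary window covered by EQ-5D: 8 / 33.7 = 24% (22% to 26%).
- Costs counted only to birth: 40 − 28 = 12 weeks (9 to 14), still longer than 8.

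Course of study puts the study start at the 29th week. With T1 at 29 weeks, the spans become 7 weeks and 32.7 weeks, which changes nothing of substance.

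**3. What could be missed.** The article does not mention QALYs; assume them here to gauge scale. Let the utility gain rise linearly from 0 at T1 to g at T5, and let W be the weeks from T5 to T7, 33.7 − 8 ≈ 26.

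- Measured gain: ½ · g · 8/52.
- Effect vanishes at T5: nothing is missed, ratio 1.
- Effect fades linearly to zero by birth at 40 weeks: ratio 1 + 4/8 = 1.5.
- Effect fades linearly to zero by T7: ratio 1 + W/8 = 1 + 26/8 = 4.25, about 4.3.
- Effect fully kept to T7: ratio 1 + 2W/8 = 1 + 52/8 = 7.5. For birth at 37 to 42 weeks (W = 22.7 to 27.7), 6.7 to 7.9.

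The ratios do not depend on g. As an illustration with g = .05: measured gain ½ · .05 · 8/52 = .0038; faded by T7, .0038 + .0125 = .0163; fully kept, .0038 + .0250 = .0288.

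**4. Which ICERs are affected.** EPDS and STAI are collected to T7, so symptom benefit on those scales can be matched to the diary window. Cesarean section is a birth event. Of the benefit measures the article names, only quality of life has this gap.

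**The case against.** The strongest reply has four parts.

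- **The long cost window is not documented for the base case.** The run to 5 months is stated only for out-of-pocket payments, which matter chiefly to the optional individual or societal perspective. The insurer perspective rests on claims data with no stated period. This stands. A reader might infer that all costs run for 34 weeks; the article does not say so. The mismatch would still remain if claims were counted only to birth.
- **The article does not prescribe a mismatched ratio.** It gives a generic ICER definition, and the horizon may be fixed in the full protocol or a health-economic plan. This also stands, so silence on the horizon is not held against the article. What is left is a data-collection choice that a later plan cannot repair: the only horizon fully covered by EQ-5D ends at week 36, before most deliveries.
- **Quality of life is one example among several benefits.** Symptom severity is named first and is followed to T7. The cost-effectiveness aim as a whole is therefore not undermined.
- **The quality-of-life hypothesis makes no postpartum claim.** A reader might infer that hypothesis (c) cannot be answered. The documents do not support that: it posits an increase in quality of life without a postpartum time point, and three antenatal measurements serve the planned 2 × 3 test.

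**Conclusion.** The point holds for the quality-of-life ICER only. That ratio would rest on 8 weeks of antenatal utility data, against about 34 weeks of diary costs (31 to 36 for birth at 37 to 42 weeks) and claims costs of unstated duration. The confirmatory tests and the symptom and cesarean ICERs are not touched.

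It is tempting to conclude that the ICER is overstated 7.5-fold. The documents do not support that as a finding. The figure is the upper end of a range from 1 to about 7.5 at birth in week 40, and it needs a QALY calculation that the article does not state, a linear rise to T5 and full persistence for 26 weeks. Reading it as an inflation of the ICER also treats the cost difference as fixed and positive, although the trial expects fewer cesareans, which could lower costs. The supportable conclusion is narrower: the size of any missed gain depends on persistence after week 36, and the trial as scheduled could not distinguish these cases. This is worth correcting because the correction is cheap and the data cannot be recovered later.

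**What to change.** Add the EQ-5D-5L, already in use at T1, T3 and T5, to the existing digital visits T6 and T7 for women not yet past them. State one common horizon for the quality-of-life ICER and compute the benefit over the same window as the costs, claims costs included. Update Table 2, and update the EQ-5D entry in Table 3, which would then have five measurements rather than three.

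Where postpartum values are unavailable, limit any quality-of-life ICER to costs accrued from T1 to T5, label it an antenatal-only result, and say that it leaves out most delivery costs and all postpartum costs. It is a fallback, not an equivalent, since delivery costs are among those the intervention is expected to change.

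The cost is a small app change and amendment, and about two minutes per woman (an estimate) at each of two visits she already completes. Recruitment began in February 2019, so women already past T6 or T7 will have no value there, and the postpartum data will be incomplete.

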### Data monitoring

Data will be monitored regularly. Sociodemographic variables are descriptively monitored on statistical parallelism with respect to mean values and standard deviations (e.g., age) or frequencies (e.g., level of education attained) to ensure comparability between the two groups. Reports from administrative monitoring are given at regular intervals.

In addition to administrative monitoring (including checks for recruitment rates), confirmatory monitoring will be carried out to ensure the study’s feasibility. *K* = 3 interim analyses (interval: *n* = 94 recruited cases) will be performed with an α-error adjusted according to Lan and Demets [62].

The independence of the evaluators is ensured via institutional and spatial segregation as well as by pseudonymization of participant data and blinding of study groups. Influences by consortia members or the sponsors on methodological procedures, data processing, and presentation of results are foreclosed. The evaluators will publish interim and final results at relevant scientific conferences and in relevant scientific peer-reviewed journals.

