**Methods:**

Within the scope of the routine prenatal care, pregnant women attending routine pregnancy care in Baden-Wuerttemberg, Germany, are invited to participate in a screening for mental distress based on the Edinburgh Postnatal Depression Scale (EPDS). Women with an EPDS screening result > 9 will be referred to one of the *mindmom* coordinating study centers and are offered counseling either face-to-face or via videotelephony. After an initial psychological counseling, women are invited to participate in an eMBI in their last pregnancy trimester. The study will enroll *N* = 280 study participants (*N* = 140 per group), who are randomized 1:1 into the intervention (IG) or control group (treatment as usual = TAU).

All participants are requested to complete a total of 7 digital assessments (5 visits pre- and 2 follow-up visits postpartum), involving self-report questionnaires, sociodemographic and medical data, physiological measures, and morning cortisol profiles. The primary outcome will be depressive and anxiety symptoms, measured by the Edinburgh Postnatal Depression Scale, the State Trait Anxiety Questionnaire, and the Pregnancy-Related Anxiety Questionnaire. Secondary outcomes include mindfulness, satisfaction with birth, quality of life, fetal attachment, bonding, mode of delivery, and cost-effectiveness.

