### Sample size

Estimation of sample size and power analysis were calculated with G*Power (Version 3.1.9.2) [32, 33]. The estimation was implemented for the confirmatory hypotheses, which aim for interaction between the between- (group) and within-subject factor (time of measurement), i.e., that the symptom burden develops differently in the two study groups over the course of time. The analysis with the lowest power is the two-factorial ANOVA with the outcome “PRAQ” (5 measurements, see Table 3, hypotheses 4–6).

The estimation is based on type 1 error of α = .016, Bonferroni-adjusted for 3 confirmatory analyses, and a power of 1 − β = .90. The statistically significant effect size is based on the results of a pilot study on mindfulness-based prevention in pregnant women with a history of depression [34]. Based on the mean values, standard deviations, and case numbers reported in this study, a final treatment effect of Cohen’s *d* = .34 (intervention group: *M* = 4.90, *SD* = 5.22, *n* = 21; control group: *M* = 6.62, *SD* = 4.94, *n* = 29) is calculated for the outcome “depressive symptoms” (EDPS score). According to Cohen (1988), this can be classified as a small effect size. Thus, the number of cases for the ANOVA design is estimated for small treatment effects (*f* = .10). Thus, *N* = 196 cases are needed to evaluate the eMBI. Assuming a dropout rate of 30%, the number of cases was determined to be *N* = 280 to reach a case number of *N* = 196 (*n* = 140 for each group or per region and *n* = 70 per group and region). With a sample size of *N* = 196, large- (*f* = .40) and medium-sized (*f* = .25) effects can be detected with a power of 1 − β = .99 and .98, respectively. Only small effects (*f* = .10) cannot be ruled out sufficiently with a power of 1 − β = .27 in case of non-significant between-subject effects.

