**Exploratory hypotheses**				
**1–9 and 14–16**	2 (group) × 3 (measurement)—ANOVA for repeated measures on the factor “measurement”	4	*F*-distribution	Group × measurement interaction effect
**10–12**	2 (group) × 2 (measurement)—ANOVA for repeated measures on the factor “measurement”	1	*F*-distribution	Group × measurement interaction effect
**13**	*t* test for independent samples	1	*t*-distribution	Group main effect
**14**	One-dimensional *χ*^2^ test with 2 cells	3	*χ*^2^-distribution	Group main effect

The critical, local α-errors for the 3 tests evaluating the confirmatory hypotheses are Bonferroni-adjusted to α_local_ = .05/3 = .016 to avoid exceeding a global α-error of α_global_ = .05 by performing multiple tests. For the exploratory analyses, the critical, local α-errors are not adjusted and set to a conventional level of α_local_ = .05. Owing to inflation of the global α-error by multiple testing (9 tests) to α_global_ = 1 − (1 − 0.05)^9^ = 0.37, the exploratory analyses have a descriptive character and will be used to generate future hypotheses.

Dunn’s multiple comparison procedure is used as a post hoc test because it allows hypothesis-driven and economic multiple testing. This procedure results in a minimum significant difference (ψ). The test value is t-distributed. As effect sizes, partial η^2^ and ω^2^ are used. These are sample-based or population-based estimators of explained variances, respectively. According to Cohen [56], η^2^/ω^2^ = .01 represents small, η^2^/ω^2^ = .06 represents medium, and η^2^/ω^2^ = .14 represents large effects.

Furthermore, identified relationships are tested for causality. This can be done by means of the study’s cross-lagged panel design (outcomes and confounding variables are collected at multiple measurement times). Here, linear structural equation modeling is used.

In order to clarify the mediating mechanisms as well as the modifiability of the identified associations, additional explorative path analyses are performed on mediating and moderating processes according to Hayes’ regression-based approach [57] using the SPSS®—macro “PROCESS” (current v. 3.4).

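### Three interim looks at 94-woman intervals do not fit an enrolment of 280; the looks are timed by recruits, .016 is not tied to the alpha spending, and interim publication has no time limit

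*Protocol article*

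**What the plan says.** Data monitoring: "K* = 3 interim analyses (interval: *n* = 94 recruited cases) will be performed with an α-error adjusted according to Lan and Demets". The purpose given there is feasibility, although the looks are called confirmatory. No spending function is named.

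Abstract, Methods: "The study will enroll *N* = 280 study participants". Sample size: "Assuming a dropout rate of 30%, the number of cases was determined to be *N* = 280 to reach a case number of *N* = 196".

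Sample size, on the error level: "type 1 error of α = .016, Bonferroni-adjusted for 3 confirmatory analyses, and a power of 1 − β = .90". Data analyses, below Table 3: the critical levels of the three confirmatory tests "are Bonferroni-adjusted to α_local_ = .05/3 = .016". Neither section mentions interim looks.

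Table 3 makes two of the three confirmatory tests 2 × 7 repeated-measures ANOVAs and the third (PRAQ) a 2 × 5 ANOVA. Course of study and Table 2 put visit 5 in the 36th gestational week and visit 7 at 5 months postpartum.

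Data monitoring, last paragraph: "The evaluators will publish interim and final results at relevant scientific conferences". Peer-reviewed journals are named as well. No condition on timing is attached.

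**The concern.** Four statements about the interim analyses do not fit together or are fixed badly.

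- **Number of looks.** Three interims at this spacing run past the enrolment total. Spending boundaries depend on how many looks there are and when they occur, so the final critical level is not determined.
- **Trigger.** A spending function works on statistical information. A count of recruits includes women whose later visits, which two of the three tests require, have not yet happened.
- **Critical level.** If alpha is spent at interims, .016 cannot be both the total for a test and the level of its final analysis. The text does not say which it is, and the power calculation treats it as a fixed-sample level.
- **Publication.** All three primary outcomes are self-reported questionnaires, and a participant knows whether she is taking the course. Comparative results made public during follow-up could influence recruitment, retention and ratings.

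At stake are the stated confirmatory error rate of .05, the stated power of .90 and the integrity of the ongoing comparison.

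**Working it through.** **1. Reproducing the plan's sample size.** From Sample size: f = .10, 2 groups, m = 5 measurements, α = .016, power .90, 30% dropout. Assumed, because not stated: correlation between measurements ρ = .5 and sphericity (ε = 1). For the group × time interaction:

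λ = f² × N × m / (1 − ρ) = .01 × 196 × 5 / .5 = 19.6, df1 = 4, df2 = 194 × 4 = 776.

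The noncentral F distribution gives power .904 at N = 196; the smallest N that reaches .90 is 194. Dropout: 196 / .70 = 280. The plan's figures reproduce, but only for a test made once at .016.

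**2. Position of the looks.** 1 × 94 = 94, 2 × 94 = 188, 3 × 94 = 282 > 280. Since 280 / 3 = 93.3, the interval looks like a third of the enrolment rounded up, with the final analysis counted as the third look.

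**3. Final level if .016 is the total per test.** Two-sided normal approximation, looks at 94/280 = .336, 188/280 = .671 and 1. The O'Brien-Fleming-type range covers the two common forms of the function: spending α/2 in each tail, or α two-sided directly. Power is that of the final test alone at N = 196.

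| Spending | Final nominal level | Power | Error per test if the final stays at .016 |
|---|---|---|---|
| O'Brien-Fleming type | .0148 to .0152 | .899 to .901 | .0167 to .0172 |
| Pocock type | .0061 | .837 | .0241 |

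Under Pocock-type spending, .90 power would need about 226 evaluable women (226 / .70 ≈ 323 recruited). This is somewhat conservative, because rejections at an interim are not counted. A simulation of the 4-df interaction as a chi-square statistic with λ = 19.6, counting rejections at any look, gives about .86 for Pocock type and .90 to .91 for O'Brien-Fleming type.

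The number of looks matters too. With three equally spaced interims plus a final, the final level would be .0146 (O'Brien-Fleming type, α/2 per tail) or .0052 (Pocock type).

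**4. Family-wise error if the final were still tested at .016.** The Bonferroni bound is 3 × .0167 = .050 to 3 × .0172 = .052 (O'Brien-Fleming type) and 3 × .0241 = .072 (Pocock type). For independent tests the Pocock-type figure is 1 − (1 − .0241)³ = .071; positive correlation lowers it.

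**5. Recruit fraction against information.** Visit 1 is in the 28th week (Table 2). Assuming birth at 40 weeks, visit 7 follows after 12 + about 22 = 34 weeks; visit 5 follows after 8 weeks. The document gives no recruitment rate, so assume steady recruitment over D weeks. Among all women, the share past visit 7 at a look is the recruit fraction minus 34/D:

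| Assumed D | Look 1 (recruits .336) | Look 2 (recruits .671) |
|---|---|---|
| 52 weeks | 0 | .02 |
| 104 weeks | .01 | .34 |
| 156 weeks | .12 | .45 |

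No woman has reached visit 7 at the first look unless D exceeds 34 / .336 ≈ 101 weeks. Equal dropout at each stage cancels from these shares. For the PRAQ test, 8/D replaces 34/D, so the lag is much smaller. Women without visit 7 still contribute earlier visits, so the table shows complete cases, not all information.

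**The case against.** Several points on the other side are sound.

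- The looks at 94 and 188 can be run. Only the third is impossible as an interim, and counting the final analysis as the third look is the natural explanation. A reader might infer that the whole interim plan is unworkable; the document does not support that.
- A reader might infer that the final tests use the full .016 as though nothing had been spent. The text does not say so. Data monitoring declares a Lan-DeMets adjustment, and .016 can be read as the per-test total to be divided over the looks. The inflated error rates in step 4 arise only if the declared adjustment is ignored at the final analysis.
- The spending function and boundaries may stand in the full protocol or the analysis plan, so their absence is no fault in itself. With O'Brien-Fleming-type spending the effect on error and power is negligible, and smaller still if the looks hold less information than the recruit fraction.
- Lan-DeMets spending can use the information actually observed, and the text does not say that the recruit fraction enters the function. Nor are the looks without outcomes: earlier recruits have some visits, and the PRAQ test needs only visit 5.
- A reader might infer publication during the trial. No timing is given, and the same paragraph describes segregated evaluators, pseudonymised data and blinded groups.

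What remains is that the article's own numbers conflict on the looks, the stated trigger does not match the outcomes of two tests, .016 is powered as a fixed level beside a spending plan, and nothing limits when interim results may appear. Blinded evaluators do not protect self-ratings once results are public.

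**Conclusion.** The point holds in a limited form. That 282 exceeds 280 is plain arithmetic: two interims and a final are the most that the stated interval allows. The recruit count overstates the information for two of the three confirmatory tests; by how much depends on the recruitment rate, which is not given. The loose link between .016 and the spending plan ranges from trivial (final level .0148 to .0152, power about .90) to material (final level .0061, final-test power about .84), depending on a function the article does not name. These figures assume ρ = .5, sphericity, .016 as the per-test total and information equal to the recruit fraction. An actual breach of the .05 error rate is not shown. The unrestricted interim publication is a real risk to the trial, but release before the trial ends is a possibility the wording leaves open, not a stated plan.

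**What to change.** In Data monitoring, state two interim analyses plus the final one. Trigger them by the number of women with the outcome data that each test requires, and compute the information fraction from those data. Name O'Brien-Fleming-type spending, and say in Sample size, Data analyses and Data monitoring that .016 is the total per test. Derive the final level from the information realised; do not fix it in advance from recruit fractions.

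Alternatively, since the stated aim is feasibility, make the looks on data pooled over the arms with no comparative test, and keep .05/3 for the final tests.

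In either case, replace the publication sentence with a rule that no comparative interim result is released before the last participant's visit 7.

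The cost is a few sentences. The power loss is below half a percentage point with O'Brien-Fleming-type spending (.904 to about .90 for the final test alone) and nil with pooled looks. Outcome-based triggers make the looks later, and comparative interim reports at conferences are given up.
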